## 3. Materials and Methods

### 3.1. Design and Sample

We embrace both quantitative and qualitative methods in this study. For the former, we use a case–control design comparable to the ex post facto prospective simple design with one independent variable (presence of disorder). For the latter, we explore the themes used by participants in their cognitive conflicts using the content analysis of their personal constructs. Using the sample size calculation program GRANMO v.7.12 (Institut Municipal d’Investigació Mèdica, Barcelona, Spain), we found that by accepting an alpha error of 0.05 and a beta error of 0.2 in a two-sided test, 78 subjects are necessary in each group to detect a small effect size between clinical and control groups, assuming a standard deviation of 1. The clinical sample will be formed by participants diagnosed with BPD receiving treatment from outpatient or inpatient public and private mental health facilities in the local area of Barcelona, Spain (CSMA *Germanes Hospitalàries*, ITA-*especialistas en salud mental*, and *ITLímit*). At the time of the first assessment, participants will be undergoing treatment as usual in each respective center, which will at least include individual psychotherapy. Non-specific or specific BPD group therapy, such as DBT or MBT, will also be part of therapeutic program of some participants. Regarding the qualitative line of this project, a content analysis system will be employed for the personal constructs of each participant, with special attention to those constructs that take part in cognitive conflicts.

#### 3.1.1. Inclusion Criteria

Individuals between 18 and 60 years old and with a diagnosis of BPD made by a well-trained professional according to DSM-5 criteria are eligible for the clinical sample. The control group is formed by healthy volunteers recruited in previous studies from 2012 to 2015, who were not receiving psychotherapy at the time of assessment. These participants will be retrieved from a student sample from the University of Barcelona [30] and a nonstudent community sample [31] and will be matched by age, gender and educational level with the clinical sample.

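### The group comparison is sized one control per patient at 78 each although controls come from existing data, so precision may be lost if more than 78 matchable controls exist

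*Protocol article*

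**What the plan says.** Section 3.1 (Design and Sample) gives a single sample size calculation, made by "accepting an alpha error of 0.05 and a beta error of 0.2 in a two-sided test". Its result is that "78 subjects are necessary in each group to detect a small effect size between clinical and control groups", "assuming a standard deviation of 1". No numeric effect is given, and no reason for equal groups.

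Section 3.1.1 (Inclusion Criteria) says where the controls come from: "The control group is formed by healthy volunteers recruited in previous studies from 2012 to 2015". They are to be retrieved from two earlier samples, one of students and one of non-students from the community, and they "will be matched by age, gender and educational level with the clinical sample". The number of people in those samples, the matching tolerance and the number of controls per patient are not given. Section 3.3 (Procedure) describes assessment sessions for patients only.

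**The concern.** Equal groups are the efficient choice when a participant costs the same in either group. Here they do not. Each patient has to be recruited, diagnosed by interview and assessed over two or three sessions, while the controls' data already exist. Patients are the scarce group, so once their number is fixed, further suitable controls lower the standard error without anyone being contacted.

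The comparison affected is the first specific objective in Section 2 and covers hypotheses 1 and 2 (presence and number of cognitive conflicts, patients against controls). It is also the comparison that Section 3.1 describes as aimed at a small effect, so any usable precision matters. There is a second reason to fix the rule. The control data were collected years ago, and the Discussion already reports on their questionnaire scores. A rule set in advance for which controls enter removes discretion over that choice.

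**Working it through.** **Inputs from Section 3.1:** two-sided alpha 0.05, power 0.80, SD 1, 78 per group. **Not in the document:** the numeric effect, the size of the control pool and the matching ratio. The ratios below are therefore assumptions, shown as a range.

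**Step 1. Reproduce the 78.** For two independent means with SD 1, n per group = 2(1.960 + 0.842)² / d² = 15.70 / d².
- d = 0.45: 15.70 / 0.2025 = 77.5, rounded up to 78. This matches.
- d = 0.20 (a common reading of small, assumed here): 393 per group. This does not match.
- d = 0.40 also gives 78, but only one-sided, and the text says two-sided.

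So 78 per group corresponds to a standardised difference of about 0.45.

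**Step 2. Hold 78 patients and vary the number of controls, m.** Standard error = √(1/78 + 1/m). Detectable difference at 80% power = 2.80 × standard error.

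| Controls per patient | m | Standard error | Detectable difference | Power at 0.45 | Power at 0.3 | Power at 0.2 |
|---|---|---|---|---|---|---|
| 1 | 78 | 0.160 | 0.449 | 80.2% | 46.6% | 23.9% |
| 1.5 | 117 | 0.146 | 0.410 | 86.8% | 53.7% | 27.7% |
| 2 | 156 | 0.139 | 0.389 | 90.1% | 58.1% | 30.2% |
| 3 | 234 | 0.131 | 0.366 | 93.1% | 63.1% | 33.4% |
| 4 | 312 | 0.127 | 0.355 | 94.5% | 65.9% | 35.2% |
| unlimited | – | 0.113 | 0.317 | 97.8% | 75.5% | 42.3% |

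These use the normal approximation. With the t distribution, the detectable differences at 1, 1.5, 2 and 3 controls per patient are 0.451, 0.412, 0.390 and 0.367, and power at 0.45 is 79.8%, 86.5%, 89.8% and 92.9%. The conclusions are the same.

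Relative to 1:1, the standard error is multiplied by √((1 + 1/k)/2) for k controls per patient. It falls 13% at 1:2, 18% at 1:3 and 21% at 1:4, and can never fall by more than 29%. Most of the gain is reached by about three per patient.

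**Step 3. Allow for unequal matching.** The table assumes the same ratio for every patient and no weights. Real matching will not be that even. As an assumed split, let 39 patients have one control and 39 have three, which makes 39 + 117 = 156 controls. Weight each control by 1 or 1/3, so that every patient's set counts once. The weights sum to 39 + 117/3 = 78 and their squares to 39 + 117/9 = 52. The effective control number is 78² / 52 = 117. The 156 controls then act like the 1.5 row (0.41), not the 2 row (0.39). The tabulated values are thus the best case for each total.

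**Step 4. Scope.** The figures are for a difference in means. Hypothesis 1 compares percentages by chi-square. More controls help there too, but the document gives no expected percentages, so no figure can be attached.

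**The case against.** The strongest reply is that the document shows no loss. The 78 is a required number from a sample size program, not a ceiling. A reader might infer that the plan caps controls at 78 and discards the rest, but nothing in Section 3.1 or 3.1.1 says so, and the ratio is left open. This stands, and it is why the point is conditional.

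The benefit also depends on an unseen number. One of the two source samples is students, and patients may be up to 60 years old. If the samples yield only about 78 usable matches, the gain is nil. This stands too. The remedy is safe in that case because it falls back to 1:1.

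Third, the matching wording may mean balance at group level rather than individual sets. This is fair, and the rule should allow for frequency matching.

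Fourth, at the effect that 78 implies, equal groups already give the planned 80% power. That is correct. It does not make extra precision worthless when the text claims to target something smaller, but it limits how serious the point is.

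A reader might also infer that using more controls would deliver the small effect that the text promises. The figures do not support this: at 0.2, power is 24% at 1:1, about 30% at 1:2 and 42% even with unlimited controls.

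Finally, more controls of the same kind narrow the interval without removing bias. They date from 2012 to 2015, and the Discussion concedes that a personality disorder cannot be fully excluded among them.

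**Conclusion.** The point holds as a conditional design recommendation. The only calculation given uses equal groups, the controls are already collected, and nothing commits the study to using all who match. If the pool has a surplus, going from one to two controls per patient cuts the detectable difference from about 0.45 to at best about 0.39, and halves the chance of missing a true difference of 0.45, from 20% to 10%. Three per patient give at best about 0.37 and 93% power.

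This rests on 78 patients being reached, on a surplus that the document does not quantify, and on near-constant ratios; uneven sets reduce the gain. It concerns hypotheses 1 and 2 only, since hypotheses 3 and 4 are tested within the patients. Whatever ratio is reached, the small-effect description does not fit the stated number and needs restating.

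**What to change.** **Section 3.1.1.** State how many people in the two earlier samples are eligible as controls, and the matching tolerance for age, gender and educational level. Specify in advance that all existing controls meeting the criteria will be used, up to about three per patient, or by frequency matching if group-level balance is intended. Where no surplus exists, the design falls back to 1:1.

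**Section 3.4.** State that the group comparisons will respect the matched sets (as strata) or use the matching weights.

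**Section 3.1.** Keep 78 as the number of patients. Replace the small-effect label with the detectable standardised difference: about 0.45 at 1:1, and at best about 0.39 at 1:2 or 0.37 at 1:3. If weights are used, compute it on the effective control number. Say that this applies to hypotheses 1 and 2 only.

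**Cost.** No new participants and no new contact. The price is a stratified or weighted analysis, plus the work of retrieving and matching further existing records. The gain may prove small if few second matches are found.

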### 3.4. Data Analysis

All data collected with the RGT will be analyzed with the program GRIDCOR 6.0 (Universitat de Barcelona, Barcelona, Spain), [43] to obtain relevant cognitive indexes, including cognitive conflict indicators. All measures derived from the RGT along with the rest of the quantitative information obtained by the rest of the instruments will be introduced and statistically analyzed with SPSS v.26 (IBM, Armnok, USA).

In order to prove the first two hypotheses, chi-square tests and variance analyses will be performed to determine whether there exist differences between groups regarding the presence, number and intensity of cognitive conflicts and, secondarily, other measures derived from the RGT. According to the obtained results, a logistic regression will be conducted to determine the capacity of the studied variables to predict group allocation. In the previous tests, and depending on the variations found between samples, relevant sociodemographic and clinical variables will be statistically controlled.

Considering only the clinical sample, correlations and analysis of variance will be performed to study the relations between cognitive variables (i.e., number and intensity of cognitive conflicts) and the clinical variables such as those retrieved from CORE-OM, DASS-21 and DIB-R scales and SCID-II BPD diagnostic criteria type and amount. Linear regression may be conducted depending on these results to assess the capacity of the studied cognitive conflict variables to predict progress one year later. In addition, based on the variability found in the sample, other variables will be statistically controlled. The study of predictive capacity of the variables with respect to treatment outcome one year later will be approached using regressions.

For the content analysis, two investigators will encode the personal constructs obtained with the RGT following the CSPC in the BPD sample. Differences in the content between congruent and discrepant constructs will be explored using chi-square tests.

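### Controls are matched on age, gender and education, but the rule for covariate adjustment tends to leave those three variables out, which can cost power in the H1/H2 tests

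*Protocol article*

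**What the plan says.** Section 3.1 describes a case–control design in which disorder status is the only independent variable, with 78 participants per group. Section 3.1.1 draws the controls from earlier studies: "The control group is formed by healthy volunteers recruited in previous studies from 2012 to 2015". It adds that they "will be matched by age, gender and educational level with the clinical sample". It does not say whether the matching is individual (pairs) or by group frequencies, and it gives no ratio.

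Section 3.4 tests the first two hypotheses (share of participants with conflicts, and number of conflicts) by chi-square tests and variance analyses. Then, according to the results, "a logistic regression will be conducted to determine the capacity of the studied variables to predict group allocation". The covariate rule for all of these is: "depending on the variations found between samples, relevant sociodemographic and clinical variables will be statistically controlled". No paired, stratified or conditional form is named.

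**The concern.** The design and the covariate rule pull in opposite directions. Matching is meant to make the groups alike on age, gender and education. A rule that adjusts where the groups differ will therefore tend to pass over exactly the variables that the matching has balanced, and the more so the better the matching succeeds.

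Balance on a variable does not make it irrelevant to the analysis. If the matching variables are related to the outcome, matched cases and controls have correlated outcomes. An independent-groups standard error ignores that correlation and is too large. The precision that the matching could have bought is then lost from the tests of H1 and H2. In a logistic model with group as the response, odds ratios that ignore the matching variables lie closer to 1 than the matched or adjusted ones.

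The rule also leaves the adjustment set for the central comparison open until the data have been seen.

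**Working it through.** **Inputs from the article (section 3.1).** The sample size rests on "accepting an alpha error of 0.05 and a beta error of 0.2 in a two-sided test", 78 per group, and "assuming a standard deviation of 1". The effect is called small, without a number.

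**Inputs assumed.** The article gives no within-pair correlation, no prevalence of conflicts, no odds ratio and no association between the matching variables and conflicts. All of these are varied below. Individual 1:1 matching is also an assumption.

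**The plan's own figure.** For two independent means, n per group = 2(1.960 + 0.842)² SD² / δ². With SD 1 and δ = 0.45 this gives 77.5, so 78. With δ = 0.2, a common reading of small, it gives 393. The stated 78 therefore corresponds to an unstated difference of about 0.45 SD, which is used here as the reference effect.

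**Means (number of conflicts), normal approximation.** The independent-groups standard error is √(2/78) = 0.160 SD. With 78 pairs and within-pair correlation ρ, the true standard error is 0.160 × √(1 − ρ). Hence:

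- ratio of the independent-groups SE to the true SE = 1/√(1 − ρ);
- true size of the nominal 5% test = 2[1 − Φ(1.96/√(1 − ρ))];
- power of the unmatched test = Φ((0.45/0.160 − 1.96)/√(1 − ρ)), where 0.45/0.160 = 2.81 before rounding;
- power of a matching-aware test = Φ(2.81/√(1 − ρ) − 1.96).

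| ρ (assumed) | SE too large by | true size | power, unmatched | power, matching-aware |
|---|---|---|---|---|
| 0 | 0% | 5.0% | 80.2% | 80.2% |
| 0.05 | 2.6% | 4.4% | 80.8% | 82.2% |
| 0.1 | 5.4% | 3.9% | 81.5% | 84.2% |
| 0.2 | 11.8% | 2.8% | 82.9% | 88.1% |
| 0.3 | 19.5% | 1.9% | 84.5% | 91.9% |

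**Proportions (presence of conflicts), simulation.** The settings were 78 pairs, control prevalence 35%, and 1,500 runs each. The columns give the share of latent variance that the matching variables explain.

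| | 0% | 7% | 23% | 41% |
|---|---|---|---|---|
| chi-square rejections, no effect | 5.3% | 3.9% | 2.8% | 2.3% |
| McNemar rejections, no effect | 5.1% | 4.1% | 4.5% | 5.0% |
| chi-square power, conditional OR 2.5 | 78.5% | 78.1% | 65.5% | 53.2% |
| McNemar power, conditional OR 2.5 | 78.3% | 80.4% | 72.9% | 67.5% |

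Compare the two tests within a column. Power falls from left to right for both because the conditional odds ratio is held fixed. Logistic regression with the matching variable as a covariate had about the same power as McNemar (78.5, 81.1, 73.1 and 67.4%).

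**Odds ratio in a model that ignores the matching variable.** By numerical integration at control prevalence 35%, a conditional OR of 3 becomes 2.95, 2.83, 2.66, 2.49 and 2.18 when the matching variables explain 2, 7, 15, 23 and 41% of latent variance. A conditional OR of 2 becomes 1.98, 1.93, 1.85, 1.78 and 1.64. If they explain nothing, nothing changes. In the simulation with conditional OR 2.5, the covariate-adjusted estimate stayed at 2.5 to 2.6 throughout.

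**The case against.** Much of the case on the other side stands.

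- **No bias in H1/H2.** A reader might infer that the main comparison is biased toward no effect. The documents do not support this. Disorder status is the explanatory factor and conflicts are the response. If matching balances the three variables, the crude differences in percentage and in mean number are not biased by them. The odds-ratio effect belongs to the logistic model, which section 3.4 makes a follow-on step for predicting group.
- **The harm is conditional and conservative.** A reader might also infer that the standard errors are wrong in any event, or that false positives rise. Neither follows. The error needs an association that the article does not quantify. It makes the tests reject too seldom, and unmatched power at 0.45 SD stays above the planned 80%.
- **Pairs are not stated.** Matching to the clinical sample can equally mean frequency matching. No McNemar or paired test is then needed, and ordinary models containing the three variables suffice.
- **The rule bars nothing.** It covers clinical variables too, and would admit age, gender or education if matching from a closed archive turned out imperfect. This stands only in part. If differences are to be found by a significance test (an assumption), 78 per group has about 24% power to flag a 0.2 SD imbalance.
- **The article is condensed.** The type of matching, its ratio and the exact model form may lie in a fuller plan, so their absence is not the point. The point is the covariate rule that the article does state, which works against its own matching.

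**Conclusion.** The concern holds as a matter of efficiency. The stated rule tends to omit the three variables on which the controls are matched, and no method that carries the matching into the analysis is named. If those variables are related to cognitive conflicts, the H1/H2 tests are conservative. With assumed pair matching and ρ of 0.1 to 0.3, the standard error is 5 to 20% too large, the true size is 3.9 to 1.9%, and power at 0.45 SD is 81 to 85% where 84 to 92% was available. When the matching variables explain up to about 7% of latent variance the loss is small; it becomes material from about 15 to 25%. The odds ratios of the follow-on logistic model would move toward 1 under the same condition. Every one of these sizes rests on assumed correlations, prevalences and odds ratios. The change is still worth making, because it costs little and does no harm if the association proves weak.

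**What to change.** Include age, gender and educational level in every between-group model for presence and for number of conflicts, whatever imbalance is observed: for example logistic regression for presence, and analysis of covariance or a count model for number. Remove the dependence on observed differences for these three variables; the rule for other variables is a separate matter. State whether matching is individual or by frequency. If it is individual, use paired or conditional methods for the H1/H2 comparisons (McNemar or conditional logistic regression for presence, a paired or mixed model for number). The follow-on model for predicting group can remain an ordinary logistic regression that contains the three variables, since a conditional model does not directly yield individual predictions of group.

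The cost is a change of wording and three or four degrees of freedom. Age, gender and education must be on record in both samples for the matching to be done, so no new data are needed.

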#### 3.1.2. Exclusion Criteria

We exclude from this study potential participants that have been diagnosed with bipolar disorder, psychotic disorder, persistent and active substance abuse, disabling physical illness, organic cerebral dysfunctions or severe mental developmental difficulties. The presence of other comorbid conditions, such as other personality disorders, anxiety disorders, eating disorders, depression or non-disabling physical illness, will not be excluded but will be recorded for statistical control. Finally, it will not be suitable to include those who do not have an enough linguistic competence to communicate in either Spanish or Catalan.

### 3.2. Instruments and Measures

#### 3.2.1. Sociodemographic Questionnaire

A sociodemographic questionnaire is used to collect data for variables such as age, gender, civil state, number of children, profession, level of education and clinical history.

#### 3.2.2. Structured Clinical Interview for DSM-IV-II (SCID-II)

The Structured Clinical Interview for DSM-IV-II (SCID-II) is a structured assessment interview aimed to identify the potential presence or absence of the personality disorders defined by the DSM-IV criteria [32].

#### 3.2.3. Diagnostic Interview for Borderlines—Revised (DIB-R)

The Diagnostic Interview for Borderlines—Revised (DIB-R) is a structured interview aimed to identify the potential presence of BPD by assessing 22 common statements for BPD patients [33,34]. It explores aspects related to affectivity, cognition, impulsivity patterns and interpersonal relationships. Zanarini et al. [35] found high levels of both inter-rater (K = 0.94) and test-retest (K = 0.91) reliability.

#### 3.2.4. Repertory Grid Technique (RGT)

The repertory grid technique is a personalized procedure using a structured interview designed to make explicit personal constructs that interviewees use to interpret and organize their interpersonal world [23,24]. It begins by identifying significant family and friends (here termed elements) and then the patient is asked to compare them (including “self now” and “ideal self”) in pairs in order to elicit the constructs used to differentiate among these elements. Once the interviewee offers a verbal tag to describe an element (e.g., “active”), they are asked to utter the opposed meaning (e.g., “passive”) to complete the bipolar dimension represented by the personal construct. Finally, the patient is asked to rate each relevant person of their interpersonal world (in addition to their actual and ideal selves) according to each personal construct expressed using a seven-point Likert scale. This creates a data matrix of elements with constructs which can be analyzed to extract several cognitive indices.

As previously mentioned, one of the main measures the RGT can provide is cognitive conflict, through the identification of implicative dilemmas and dilemmatic constructs. In order to detect the presence of implicative dilemmas, first we need to identify both congruent and discrepant constructs. The former ones are defined by the congruence between the scores of the “self now” and “ideal self” elements in that construct (e.g., being a “protector” in the example of Feixas et al. [36]), and the latter by a dissonance (or dissimilarity) between these two elements, indicating a discrepancy in the way individuals perceive themselves and how they would desire to be (e.g., not “loving herself” but wishing to do it, in the same case example). An implicative dilemma is detected when a correlation between the scores of a congruent construct and a discrepant construct is found, when the direction that the desired change indicated by the discrepant construct is associated with the loss of congruence for the self (e.g., “loving herself” is associated with being “unemotional”, the opposite pole of being a “protector”). Therefore, discrepant constructs per se do not define a conflict or dilemma but are just a discrepancy (see other measures below), a target for change. 

“Rather, it is the conflictive association between a discrepant and a congruent construct which causes conflict. In these cases, the need for change (she wants to love herself) might be hindered by the need for self-ideal congruency (continue being protective). What an implicative dilemma tells us is that the need for change expressed by the discrepant construct is in conflict with the need for coherence expressed by the congruent construct. Thus, the patient unwittingly hesitates in taking a clear course of action because striving for loving herself has negative implications for her identity. In the view of such a dilemma, change may be less likely to occur because abandoning the symptoms would result in invalidation of core aspects of the self.” [36] (p. 372)

On the other hand, dilemmatic constructs are detected when the patient does not have a preference for neither pole of a personal construct and therefore indicates a middle point in the rating for the ideal self. In this situation, the individual may have doubts regarding the best position they could take in a specific personal construct, thus experiencing another type of dilemma in a construct for which each pole might involve both positive and negative implications for the self. Examples of implicative dilemmas and dilemmatic constructs can be found in Feixas et al. [36] and Paz et al. [37]. 

Other than these types of cognitive conflicts, the analysis of the RGT data matrix provides the following measures:Self-discrepancies: These measures are calculated through Euclidean distances between the elements “self now”, “ideal self” and “others” (considered as the mean of all elements other than the selves).
○Self-ideal discrepancy: Higher distances between “self now” and “ideal self” are usually interpreted as low self-esteem.○Self-others discrepancy: While high scores indicate perceived social isolation, low scores point out a high level of identification with others.○Ideal-others discrepancy: Conceived to measure perceived adequacy of significant others, large distances indicate a critical view of others.Interpersonal dichotomous thinking: Computing the total amount of extreme scores (“1” and “7”) yields the polarization index. This measure reveals if there is a tendency towards dichotomous thinking (all or nothing) when construing self and others.Interpersonal cognitive differentiation: This domain is measured through the percentage of variance accounted for the first factor (PVAFF), an index that results from the correspondence analysis of the whole grid data matrix. A large size of the first factor indicates a tendency to interpret interpersonal experiences in a unidimensional way, while a low PVAFF allows for a more differentiated view, with more nuances, suggesting that multiple points of view are available when construing self and others.

